### Superficial incisional SSI

A case will be classified as superficial incisional SSI if all of the following conditions are met:

1. The infection occurs within 30 days postoperatively.
2. The infection is limited to the skin and subcutaneous tissue.
3. At least one of the following criteria is met:
4. Purulent discharge from the superficial incision.
5. Organisms isolated from aseptically obtained fluid or tissue from the superficial incision.
6. The superficial incision is deliberately opened by the surgeon, with or without positive culture, and at least one of the following symptoms is present: pain, tenderness, localized swelling, erythema, or heat. A negative culture result does not meet this criterion.
7. The attending physician or surgeon diagnoses the condition as superficial incisional SSI.

### Deep incisional SSI

A case will be classified as deep incisional SSI if all of the following conditions are met:

1. The infection occurs within 30 days postoperatively.
2. The infection involves deep soft tissues, such as fascia and muscle layers.
3. At least one of the following criteria is met:
4. Purulent discharge from the deep incision, excluding the organ/space.
5. The deep incision spontaneously dehisces or is deliberately opened by the surgeon, with or without positive culture, and at least one of the following symptoms is present: fever (>38°C), localized pain, or tenderness. A negative culture result does not meet this criterion.
6. An abscess or other evidence of infection involving the deep incision is detected via direct examination, reoperation, histopathology, or radiologic imaging.
7. The attending physician or surgeon diagnoses the condition as deep incisional SSI.

### Organ/Space SSI

A case will be classified as organ/space SSI if all of the following conditions are met:

1. The infection occurs within 30 days postoperatively and is deemed to be related to the surgical procedure.
2. The infection involves any part of the body that was manipulated during the surgery, excluding the incision, fascia, or muscle layers.
3. At least one of the following criteria is met:
4. Purulent discharge from a drain placed in the organ/space through a stab wound.

Organisms isolated from aseptically obtained fluid or tissue samples from the organ/space.

1. An abscess or other evidence of infection involving the organ/space is detected via direct examination, reoperation, histopathology, or radiologic imaging.
2. The attending physician or surgeon diagnoses the condition as organ/space SSI.

# Adverse Events and Study-Related Conditions

## Definition and Management of Adverse Events and Study-Related Conditions

An adverse event (AE) is defined as any unfavorable or unintended disease, injury, or medical condition that occurs in a study subject, regardless of its causal relationship with the study. Under the Japanese Clinical Trials Act, "study-related conditions" refer to adverse events where a causal relationship with the study intervention cannot be ruled out.

Adverse events occurring from the start of the study until the end of the observation period (30 days postoperatively or the later of discharge/transfer) will be reported. If an adverse event meeting the definition of a study-related condition occurs after the observation period, it will also be reported.

If an adverse event occurs, the principal investigator or sub-investigators must take appropriate measures and monitor the patient’s progress. Details of adverse event management are outlined in the Procedures for Handling Study-Related Conditions (see Appendix).

## Definition and Management of Serious Adverse Events and Study-Related Conditions

Serious adverse events include any of the following:

1. Death
2. Life-threatening events
3. Permanent disability
4. Events that may result in permanent disability
5. Hospitalization or prolonged hospitalization due to treatment
6. Other events deemed serious
7. Congenital anomalies in future generations.

If a serious adverse event occurs, the principal investigator or sub-investigators must take appropriate measures and follow the "Procedures for Handling Study-Related Conditions." The event must be reported immediately to the CRB, institutional administrators, and the lead investigator.

If the event is deemed a study-related condition, the lead investigator will report it to the Minister of Health, Labour and Welfare (via the Pharmaceuticals and Medical Devices Agency), institutional investigators, and the device provider in accordance with the Japanese Clinical Trials Act.

## Management of Device Malfunctions

If a malfunction occurs in the study device, the principal investigator or sub-investigator must report it to the institutional principal investigator. The institutional principal investigator must notify the institutional administrator and the lead investigator. If the malfunction is deemed to pose a risk of a serious adverse event, the lead investigator will report it to the CRB within 30 days of becoming aware of the issue. If a serious adverse event occurs due to the malfunction, management will follow the procedures outlined in 10.2.

## Expected Adverse Events

According to the latest package insert for the 3M™ Prevena Plus Customizable Kit, serious adverse events such as bleeding and infection have been reported. Device malfunctions include fire and false alarms. Other adverse events include allergic reactions, maceration, lymphatic leakage, epidermal necrosis, delayed or worsened wound healing, soft tissue damage, contact dermatitis, blisters, abscesses or cellulitis, swelling, pressure ulcers, wound dehiscence, hematoma, and seroma.

# Expected Benefits and Risks/Discomfort Associated with Study Participation

## Expected Benefits

1. Reduction of perineal wound SSI, potentially leading to shorter hospital stay, reduced medical costs, and improved patient quality of life (QOL).
2. Prevention of delays in initiating postoperative adjuvant chemotherapy, potentially leading to improved curability of rectal cancer and enhanced long-term prognosis.

## Burdens and Potential Risks

1. Delayed detection of wound infections due to pNPWT application, potentially leading to progression of superficial incisional SSI to deep incisional SSI or organ/space SSI.
2. Skin damage caused by the application and removal of the pNPWT foam filler, including epidermal detachment and erosion.
3. Increased discomfort in the perineal and gluteal regions due to pNPWT application.

## Measures to Minimize Burdens and Risks

Regular monitoring will be conducted to evaluate adverse events and other safety concerns.

# Statistical Analysis

## Analysis Population

### Safety Analysis Set (SAS)

The safety analysis set (SAS) will include all enrolled patients who had the investigational device applied, even partially.

### Efficacy Analysis Set (EAS)

The efficacy analysis set (EAS) will include all enrolled patients who had the investigational device applied and did not violate major study protocol criteria (e.g., failure to meet inclusion criteria, lack of consent, unregistered cases, or other significant procedural violations).

## Analysis Methods

### Primary Analysis

1. Incidence of Perineal Wound SSI

The proportion of patients who develop perineal wound SSI will be calculated along with the 95% confidence interval.

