## Development of This Study Plan

In March 2021, the Prevena Incision Management System (IMS) (3M, St. Paul, Minnesota) became the first pNPWT device approved in Japan. Prior to this clinical trial, a preliminary study was conducted at Fukuoka University Hospital, where Prevena was applied to perineal closed wounds after APR. In a control group of 117 patients who underwent primary closure alone without pNPWT, perineal wound SSI was observed in 24%. In contrast, in the pNPWT group (10 patients), no cases of perineal wound SSI were reported.

This study aims to prospectively evaluate the safety and effectiveness of pNPWT for perineal closed wounds after APR, thereby clarifying its effectiveness, indications, and clinical significance. Since April 2022, pNPWT has been covered by the Japanese insurance system, and its use for SSI prevention in high-risk patients may become the standard of care. The data obtained in this study will provide the basis for a future large-scale trial in gastrointestinal surgery, further establishing the efficacy and safety of pNPWT for perineal and other surgical wounds.

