# Study Design

## Overview of Study Design

This study is a multicenter, single-arm, open-label, non-controlled interventional trial.

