## Target Sample Size and Rationale for Determination

The target sample size for this study is 50 patients.

< Rationale for Sample Size Calculation >

Existing reports indicate that the incidence of perineal wound SSI in patients receiving pNPWT ranges from 9.1% to 14.8%, whereas the incidence in patients not receiving pNPWT ranges from 32.6% to 41.7% ^(18,20)^. This study assumes that the incidence of perineal wound SSI within 30 days postoperatively will be 12%, with a threshold of 40% based on prior reports. Given a two-sided significance level of 5% and a power of 80%, the required sample size is 45 patients. To account for potential dropouts, the planned enrollment target is set at 50 patients.

< Estimated Patient Accrual >

The participating institutions collectively treat approximately 80 patients per year who meet the eligibility criteria. Assuming an eligibility rate of 70% and a consent rate of 70%, it is expected that 50 patients can be enrolled within 15 months.

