## Early Termination, Suspension, and Resumption of the Study

The principal investigator shall evaluate the feasibility of continuing the study under the following circumstances:

1. When critical information regarding safety or efficacy is obtained.
2. When difficulties in recruiting study participants make it unlikely to achieve the planned sample size.
3. When the study objectives are achieved before reaching the planned sample size or study duration.
4. When the number of cases of perineal surgical site infection (SSI) exceeds 20 (i.e., when the incidence of perineal SSI exceeds 40%, surpassing the previously reported incidence in the non-pNPWT group).
5. When the administrator of the implementing medical institution, upon receiving the opinion of the CRB, issues an instruction to modify the research plan, and compliance with such modification is deemed unfeasible.

If the administrator of the implementing medical institution, based on the opinion of the CRB, recommends or instructs the termination of the study, the study shall be discontinued.

If the study is terminated or suspended early, regardless of the reason, the principal investigator or sub-investigators shall promptly notify all study participants and take appropriate measures to ensure their safety, including conducting necessary medical examinations.

The principal investigator shall notify the Certified Clinical Research Review Board of the termination within 10 days of the termination date and report it to the Minister of Health, Labour and Welfare. Additionally, a report shall be submitted to the administrator of the implementing medical institution.

To resume a suspended clinical study, a report must first be submitted to the CRB, followed by obtaining approval from the administrator of the implementing medical institution. Thereafter, the study shall be reported to the MHLW before resumption.

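### The 80% power stated for 45 patients does not fit a single-arm test of 12% against 40%, where power is about 99%, and the primary analysis never ties its interval to the 40%

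*Protocol*

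**What the plan says.** The design (section 6.1) has one arm: "This study is a multicenter, single-arm, open-label, non-controlled interventional trial".

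The sample-size rationale (section 12.3) is worded as a hypothesis test. It assumes that "the incidence of perineal wound SSI within 30 days postoperatively will be 12" per cent, "with a threshold of 40% based on prior reports", and concludes: "Given a two-sided significance level of 5% and a power of 80%, the required sample size is 45 patients". Then: "To account for potential dropouts, the planned enrollment target is set at 50 patients". It names no formula and no dropout rate; going from 45 to 50 implies 5/50 = 10%.

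The primary analysis (section 12.2.1) is one sentence: "The proportion of patients who develop perineal wound SSI will be calculated along with the 95% confidence interval". It gives no null value, no interval method and no link to 40%. The objective (section 2) and the primary outcome (section 9.1) add no criterion for effectiveness.

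The 40% appears once more, in section 17.2, among the circumstances for reviewing whether to continue: "When the number of cases of perineal surgical site infection (SSI) exceeds 20". That concerns continuation and is not an efficacy criterion.

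**The concern.** A power figure belongs to a specific test. Section 12.3 gives a significance level, a power and a threshold, while section 12.2.1 plans an estimate with an interval and does not mention the threshold. Two questions follow: is 80% the power of the test that the planned interval implies, and does the protocol say how that interval will be read?

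At stake is whether the stated basis for enrolling 50 patients is correct, and whether a result near the boundary has one defined reading before the data are seen.

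**Working it through.** **Inputs (section 12.3).** Expected rate p₁ = 0.12, threshold p₀ = 0.40, difference d = 0.28, two-sided 5% (z = 1.960), 80% power (z = 0.8416), stated n = 45, enrolment 50.

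**1. Reproducing 45.** Take the two-arm comparison of proportions with pooled variance under the null, p̄ = (0.40 + 0.12)/2 = 0.26:

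n = [1.960·√(2·0.26·0.74) + 0.8416·√(0.40·0.60 + 0.12·0.88)]² / 0.28²
= [1.960·0.6203 + 0.8416·0.5879]² / 0.0784 = 1.7106² / 0.0784 = 37.3, so 38 per arm.

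With continuity correction:

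n′ = (n/4)·[1 + √(1 + 4/(n·d))]² = 9.331·[1 + √(1 + 4/10.45)]² = 9.331·2.176² = 44.2, so **45 per arm**.

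This matches the stated number, but it is the size of each of two arms.

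**2. Single-arm calculation with the same inputs.**

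- Score test: n = {[1.960·√(0.40·0.60) + 0.8416·√(0.12·0.88)] / 0.28}² = {[1.960·0.4899 + 0.8416·0.3250] / 0.28}² = 4.406² = 19.4, so 20.
- Exact binomial, lower tail at most 0.025 under 40%:

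| n | Success if SSIs at most | Tail probability at 40% | Power at 12% |
|---|---|---|---|
| 19 | 3 | 0.0230 | 81.3% |
| 20 | 3 | 0.0160 | 78.7% |
| 23 | 4 | 0.0190 | 86.7% |

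Exact power first reaches 80% at n = 19, dips below it from 20 to 22, and stays above it from 23. The single-arm answer is therefore about 19 to 23 patients.

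**3. Power at the planned size.** A Clopper-Pearson upper limit below 40% is the same as P(X ≤ x | 0.40) < 0.025.

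| n | Last success (upper limit) | First failure (upper limit) | P(success) at 40% | Power at 12% |
|---|---|---|---|---|
| 45 | 11 (39.5%) | 12 (41.9%) | 0.0216 | 99.4% |
| 50 | 12 (38.2%) | 13 (40.3%) | 0.0133 | 99.5% |

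**4. Does the unnamed interval matter?** At n = 45 the Wilson interval gives the same cut-off of 11. At n = 50 it does not: 13/50 has a Wilson upper limit of 39.6% (pass) and a Clopper-Pearson upper limit of 40.3% (fail). The Wilson rule at 50 has a lower-tail error of 0.0280, slightly above 0.025, and power of 99.8%.

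**5. What the spare power would allow.** Section 12.3 cites 32.6% to 41.7% without pNPWT. With 32.6% as the threshold and 50 patients, success is at most 9/50 (Clopper-Pearson upper limit 31.4%; 10/50 gives 33.7%), and power at 12% is P(X ≤ 9) = 92.9%.

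**The case against.** **The interval already is the test.** A two-sided 95% interval can be inverted into a two-sided 5% test, and section 12.3 supplies the 40%. This stands. It would be wrong to infer that the power belongs to an analysis that is never done. What is missing is a linking sentence and the interval method. But reading the interval against 40% is exactly what gives 99%, so this defence does not rescue the 80%.

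**A SAP may supply the rule.** Interval method and cut-off counts are often left there, and their absence alone would not be a point. The power figure, however, is a protocol statement that does not fit the protocol's own design and inputs, whatever a SAP adds. The missing link is raised because no power can be stated without it.

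**Any observed rate below 40% could be called effective.** A reader might infer this from the silence of section 12.2.1. The documents do not support it. Nothing says that a point estimate suffices, and 15/50 (30%), for example, has an exact interval of 17.9% to 44.6%, which does not exclude 40%. The real ambiguity is narrow, as at 13/50.

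**The rule would accept an untreated rate.** Section 1.3 reports for patients without pNPWT that "perineal wound SSI was observed in 24" per cent, and 12/50 is also 24%. A reader might infer that the rule passes a result no better than no treatment. That control group of 117 came from one hospital and is not said to meet the high-risk criteria every trial patient must meet. It is context, not the untreated rate for this population.

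**Little harm follows.** This is a phase 2 study meant to inform a larger trial, and it has ample power against 40%. That stands, and it limits the weight of the point.

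**Conclusion.** The point holds in this form. For the single-arm design and the stated inputs, 45 patients do not correspond to 80% power. Power at a true rate of 12% is 99.4% with 45 and 99.5% with 50, and about 19 to 23 patients would give 80%. Section 12.2.1 does not link its interval to 40% or name the method, so one outcome at full enrolment (13/50) has no fixed reading.

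These figures assume the exact 95% upper limit below 40% as the rule, which the protocol implies but does not state. A Wilson interval leaves power above 99%.

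That 45 came from a two-arm formula is an inference from an exact numerical match. It is not the only possible source: an exact single-arm calculation of 20% against 40% also first reaches 80% power at 45, but it departs from the stated 12%.

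A reader might take the error to mean that the trial is too small. It is not: against 40% the size is more than enough. The error lies in the stated justification and the open reading of the result.

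**What to change.** **Section 12.2.1.** Add: *The null hypothesis is that the perineal SSI proportion is 40% or more. pNPWT is regarded as effective only if the upper limit of the two-sided 95% Clopper-Pearson interval is below 40%, that is, with at most 11 SSIs in 45 evaluable patients or 12 in 50.* Give the matching count for any other evaluable number.

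**Section 12.3.** Replace the 80% and the derivation of 45 with the single-arm exact calculation: about 99% power at 12% with 45 to 50 evaluable patients. Name the method and keep 50 as the enrolment target.

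**Optional.** Note that the spare power would support a stricter threshold at the low end of the cited untreated range (32.6%: at most 9/50, 93% power at 12%). If the sponsor chooses it, 12.2.1 and 12.3 must carry the same value.

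**Cost.** A few sentences and no additional patients. Under section 12.4 a change to the analysis plan means a protocol revision with its approvals. The only statistical downside is that the sponsor commits to a cut-off in advance.

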### Secondary Analyses

#### Efficacy Analyses

1. Incidence of postoperative complications other than perineal wound SSI

The proportion of patients experiencing Clavien-Dindo Grade III or higher complications will be calculated along with the 95% confidence interval.

1. Postoperative length of hospital stay

The median and interquartile range of postoperative hospital stay will be calculated.

1. Completion rate of pNPWT

The proportion of patients who successfully maintained pNPWT for 7 days postoperatively will be calculated along with the 95% confidence interval.

#### Safety Analysis

The number and proportion of patients experiencing adverse events or study-related conditions will be reported.

## Target Sample Size and Rationale for Determination

The target sample size for this study is 50 patients.

< Rationale for Sample Size Calculation >

Existing reports indicate that the incidence of perineal wound SSI in patients receiving pNPWT ranges from 9.1% to 14.8%, whereas the incidence in patients not receiving pNPWT ranges from 32.6% to 41.7% ^(18,20)^. This study assumes that the incidence of perineal wound SSI within 30 days postoperatively will be 12%, with a threshold of 40% based on prior reports. Given a two-sided significance level of 5% and a power of 80%, the required sample size is 45 patients. To account for potential dropouts, the planned enrollment target is set at 50 patients.

< Estimated Patient Accrual >

The participating institutions collectively treat approximately 80 patients per year who meet the eligibility criteria. Assuming an eligibility rate of 70% and a consent rate of 70%, it is expected that 50 patients can be enrolled within 15 months.

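### Section 12.3 says 80% power requires 45 patients, but its own inputs give about 20 for a single-arm test, and 45 gives about 99% power.

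*Protocol*

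**What the plan says.** Section 6.1 fixes the design: "This study is a multicenter, single-arm, open-label, non-controlled interventional trial".

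Section 12.3 quotes SSI rates from earlier reports. The rate with pNPWT "ranges from 9.1% to 14.8%, whereas the incidence in patients not receiving pNPWT ranges from 32.6% to 41.7"%. From these it assumes that the incidence within 30 days "will be 12%, with a threshold of 40% based on prior reports". It then states: "Given a two-sided significance level of 5% and a power of 80%, the required sample size is 45 patients". Finally: "To account for potential dropouts, the planned enrollment target is set at 50 patients". No dropout rate is given; 45/50 implies 10%.

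Section 12.3 names no test, formula or software. Section 12.2.1 plans the primary analysis as one proportion with a 95% confidence interval.

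**The concern.** Section 12.3 gives every input that a one-sample size needs (expected rate, fixed threshold, error level and sidedness, power), and it also gives the result. The result does not follow from the inputs. The threshold is a fixed number taken from the literature, so no sampling error from a control group has to be paid for, and a gap of 28 percentage points should need far fewer than 45 patients.

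The number of patients described as required, and the power attached to it, are what a review board and a later reader rely on to judge the trial's size. If both are wrong, the stated justification for exposing 50 patients is not the real one. A reader would also misjudge what a result below 40% means, believing that the trial had a one-in-five chance of missing the expected effect.

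**Working it through.** **Inputs** (section 12.3 unless noted): expected rate p1 = 0.12; threshold p0 = 0.40; difference 0.28; two-sided 5% (z = 1.960); power 80% (z = 0.8416); one arm (section 6.1).

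**1. Reproducing 45.** Only a two-group formula returned it. With the mean rate (0.12 + 0.40)/2 = 0.26:

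- Pooled, uncorrected: m = [(1.960·√(2·0.26·0.74) + 0.8416·√(0.40·0.60 + 0.12·0.88)) / 0.28]² = [(1.2158 + 0.4948)/0.28]² = 37.3, so 38 per group.
- With continuity correction: (m/4)·[1 + √(1 + 4/(m·0.28))]² = 9.33·(1 + √1.3828)² = 44.2, so **45 per group**, or 90 in total.

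Other uncorrected two-group versions give 35 (unpooled) and 36 (arcsine).

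**2. One-sample size, normal approximation.**

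n = [(1.960·√(0.40·0.60) + 0.8416·√(0.12·0.88)) / 0.28]² = [(0.9602 + 0.2735)/0.28]² = 19.4, so **20**.

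The other one-sample approximations tried give 11 (Wald), 18 (arcsine), 23 (continuity-corrected) and 25 (null variance throughout). None comes near 45.

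**3. One-sample size, exact binomial.** For each n, take the largest count c with P(X ≤ c | 0.40) ≤ 0.025. The power is then P(X ≤ c | 0.12).

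| n | c | attained one-sided error | power at 12% |
|---|---|---|---|
| 19 | 3 | 2.3% | 81.3% |
| 20 | 3 | 1.6% | 78.7% |
| 21 | 3 | 1.1% | 76.0% |
| 22 | 3 | 0.8% | 73.3% |
| 23 | 4 | 1.9% | 86.7% |
| 45 | 11 | 2.2% | **99.4%** |
| 50 | 12 | 1.3% | **99.5%** |

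Power first reaches 80% at 19, dips below it at 20 to 22 because the counts are discrete, and stays above it for every n from 23.

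**4. Sensitivity to the expected rate.** At 14.8%, the highest pNPWT rate quoted in section 12.3, exact power against 40% with 45 patients is still 97.3%. At a true rate of 20% it is 82.6%.

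**5. Precision.** An observed 6/50 (12%) has an exact 95% confidence interval of 4.5% to 24.3%.

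**The case against.** Four points can be made for the plan.

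- **The error is conservative.** The trial has more power against 40% than it claims, not less. This stands, and it limits the consequence: nobody should infer that the trial is underpowered against its threshold. It does not make the stated figures true.
- **The primary analysis is an estimate with a confidence interval, with no test or rejection count stated.** This also stands. The estimate and interval in section 12.2.1 do not depend on the power figure, and 45 to 50 patients can be defended on precision. But section 12.3 does not make that argument; it says that 45 are required for 80% power. The rejection counts above are derived here from the stated 5% level and are not quoted from the protocol.
- **The test may be described in a statistical analysis plan that is not shown.** That could supply a missing detail. Here nothing is missing: the inputs and the result stand together in section 12.3 and disagree.
- **The two-group origin is an inference.** Correct. A reader might conclude that the sponsor certainly used a two-arm formula. The protocol names none, and only the pooled version with continuity correction gives 45; the uncorrected ones tried give 35 to 38. The coincidence makes it the likely source and no more. The finding does not need it, because 45 fails as a one-sample size whatever its origin.

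**Conclusion.** The point holds as an error in the stated rationale. For a single-arm test of 12% against a fixed 40% at two-sided 5%, 80% power needs about 20 patients (normal approximation) or 19 to 23 (exact; reliably from 23), roughly half of the 45 stated. With 45 patients the exact power is 99.4%, about 19 points above the stated 80%. This rests on reading the two-sided 5% as 2.5% in the lower tail and 40% as a fixed value, as section 12.3 presents it.

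Two stronger readings are tempting and not supported. One is that the sponsor does not know what the trial can detect: the document shows a wrong figure, not what anyone knows. The other is that the spare power shows a stricter threshold, such as 30%, to be affordable with the same patients. That value lies below the 32.6% to 41.7% quoted in section 12.3 for patients without pNPWT. With 45 patients, exact power against 30% (at most 7 SSIs) is 83% at 12% but only 65% at 14.8%, which is within the protocol's quoted pNPWT range. The choice of threshold is a separate matter.

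**What to change.** Keep the enrolment target of 50 and rewrite the rationale in section 12.3 in one of two ways.

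- **As a test.** Name the exact one-sample binomial test against 40%. Give the rejection count, the attained one-sided error and the power at a true rate of 12%, both for 45 evaluable patients (at most 11 SSIs; 2.2%; 99.4%) and for 50 (at most 12 SSIs; 1.3%; 99.5%). Say that about 20 to 23 patients would suffice for 80% power and why more are enrolled.
- **As precision.** Justify 45 to 50 patients by the width of the 95% confidence interval that section 12.2.1 plans, for example about 4.5% to 24.3% at 6/50, and remove the statement that 45 are required for 80% power.

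Either way, state the assumed dropout rate (10% if 50 is to leave 45). The cost is a protocol wording change with the usual board approval. It needs no extra patients, visits or data.
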